# Optimising Prescription of Treatment In older patients with Mild hypertension at Increased risk of Serious adverse Events (OPTIMISE2): protocol for a primary care based, open-label, randomised controlled non-inferiority trial

**DOI:** 10.1186/s13063-026-09508-7

**Published:** 2026-02-14

**Keywords:** Randomised controlled trial, Blood pressure, Deprescribing, Medication discontinuation, Serious adverse events, Primary care, Aged, Frailty, Mortality, Cardiovascular disease

## Abstract

**Background:**

Antihypertensive treatment is effective at reducing the risk of cardiovascular disease, but is associated with adverse events, particularly in older patients with frailty. As a result, deprescribing antihypertensive medications is recommended in some clinical guidelines despite limited evidence from a few small randomised controlled trials. The aim of the OPTIMISE2 trial is to examine the safety, efficacy and cost-effectiveness of deprescribing antihypertensive treatment in older adults with controlled systolic blood pressure, who are at higher risk of adverse events.

**Methods:**

The OPTIMISE2 trial aims to enrol 3014 participants into the trial and actively follow them up for 1 year. Participants are aged 75 years and above and taking two or more blood pressure lowering drugs, with controlled blood pressure readings (systolic blood pressure < 140 mmHg if aged 75–79 years or < 150 mmHg if aged 80+ years), frail and/or at a higher risk of serious drug-related side effects of hypotension, syncope and falls. The trial randomises (1:1) participants to either step-down medication reduction (withdrawal of one antihypertensive medication at a time, at 4-week intervals with regular monitoring of blood pressure) or usual care (no medication reduction mandated). The choice of medications to withdraw is at the discretion of participating general practitioners or prescribers. The primary outcome is emergency hospitalisation or death within 1 year of randomisation. The primary objective is to determine whether antihypertensive deprescribing is non-inferior to usual care, with up to a 5% difference in the percentage of patients with an emergency hospitalisation/death. The study uses a within-trial economic evaluation and decision-analytic modelling to estimate the cost-effectiveness of deprescribing antihypertensive treatment.

**Discussion:**

It is expected that these findings will inform clinical guidelines and practice about deprescribing of antihypertensive medications in older adults with frailty, who have controlled systolic blood pressure but are at higher risk of adverse events.

**Trial registration:**

ISRCTN18030225. Registered on 19/09/2023.

Secondary Identifying Numbers: University of Oxford Sponsor Protocol Number 16667. IRAS 1006598. CPMS 56390.

**Supplementary Information:**

The online version contains supplementary material available at 10.1186/s13063-026-09508-7.

## Background

In England, approximately 1.5 million adults aged over 75 are prescribed five or more medications [1, 2] to treat their long-term conditions, a situation described as polypharmacy. Inappropriate polypharmacy (where patients are prescribed too many medications for the conditions present) [3] is associated with reduced independence and quality of life, and an increased likelihood of hospital admissions for drug-related adverse events [4, 5]. One approach to managing polypharmacy is to deprescribe medications which may no longer provide benefit or where the chance of adverse events is high. Deprescribing is the process of withdrawing or reducing the use of medications that are considered inappropriate or unnecessary for a particular patient, supervised by a health care professional, to improve health outcome [6].

Drugs to manage blood pressure are highly effective at reducing the risk of cardiovascular disease [7, 8] and are the most frequently prescribed medication in patients with polypharmacy [1]. However, they are also associated with potential harm [7], increasing the risk of hypotension, syncope, acute kidney injury and electrolyte abnormalities, and these adverse effects are more likely in older patients and those with increasing frailty [7, 8]. As a result, clinical judgement is encouraged when prescribing antihypertensive treatment in older adults with frailty [9], and deprescribing antihypertensive medications is now recommended in some clinical guidelines [10] despite limited evidence from only a few small randomised controlled trials.

The University of Oxford team previously completed the largest trial of blood pressure medication reduction to date, enrolling 569 participants and following them up for 12 weeks. This study demonstrated that deprescribing antihypertensives was non-inferior to usual care with regard to blood pressure control (RR 0.98, 95% CI 0.92 to ∞), albeit with an increase in mean systolic blood pressure of 3 mm Hg at 12 weeks [11]. Long-term follow-up via participants’ electronic health records found no evidence of an association between deprescribing and all-cause hospitalisation or mortality [12]; however, this trial was not powered to determine the long-term effects of deprescribing on clinical outcomes. Therefore, it is not currently known if deprescribing is safe or effective in the longer term. This trial examines the effect of antihypertensive deprescribing on clinical outcomes related to benefit and harm, health-related quality of life and costs to the NHS.

### Trial design

This trial uses an individually randomised, controlled, non-inferiority design, based on the trial design successfully tested and implemented in the previous OPTiMISE trial [11, 13, 14]. It aims to establish whether deprescribing antihypertensives is safe in older people, examining the following research questions:What is the effect of deprescribing blood pressure lowering drugs on hospital admissions and death?What is the effect of deprescribing on costs to the NHS and health-related quality of life?

The trial compares step-down medication reduction (withdrawal of one antihypertensive medication at a time, at 4-week intervals, with monitoring of blood pressure at 4 weeks’ visit following each withdrawal) with usual care (no medication reduction mandated). Participants are expected to attend a baseline visit and a 4-week safety visit per antihypertensive deprescribed. Subsequent follow-up data is collected via routine electronic health records and participant questionnaires sent at 1-year post-randomisation. The primary outcome is emergency hospital admission and all-cause death at 1 year. The trial team will also perform a cost-effectiveness analysis to assess the short and long-term impacts of deprescribing antihypertensives.

This trial is undertaken in a primary care setting, within approximately 200 general practices across all regions of the NIHR Research Delivery Network in England. The primary care setting enables all potentially eligible participants to be identified and approached, and permits examination of the intervention, in the setting in which it will be delivered in routine clinical practice.

### Trial outcomes

The primary outcome is all-cause emergency hospitalisation or death during the 12 months following randomisation. This is determined using health record data obtained from NHS England using ‘method of admission’ codes 21–25 and 28 (admission for at least 1 day overnight) or death, and from practice-reported serious adverse events. Secondary outcomes are major cardiovascular events, a cardiovascular death, all-cause death, all-cause emergency hospitalisation, all-cause hospitalisation, acute myocardial infarction, stroke, heart failure, serious falls, fractures, hypotension, syncope, dementia, a serious adverse event, a non-serious adverse event, an adverse drug withdrawal event, or admission to a nursing home or care facility between groups. Further secondary outcomes are to determine the difference in average treatment burden, average medication burden, and average antihypertensive medication between groups and those in the intervention arm who maintain medication reduction through to follow-up. The trial also measures the difference in average blood pressure and the percentage of participants experiencing symptoms such as dizziness, fatigue and ankle swelling, using the Beliefs about Medicines Questionnaire (BMQ) General [15]. The EuroQol 5-Dimension 5-Level Questionnaire (EQ-5D-5L) [16] index is used to determine the difference in health-related quality of life between randomised groups and the Katz Activities of Daily Living – Life Ability Questionnaire [17] is used to determine the percentage of participants with a physical disability between groups.

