### Baseline assessments

After consent, participants undergo baseline procedures with a research nurse, or other appropriately trained and delegated member of the team, including measurement of clinic blood pressure readings. Blood pressure is taken after participants have been seated for 5 min of rest using a clinically validated blood pressure monitor, and the mean of the 2nd and 3rd readings is used the define trial eligibility. To test for orthostatic hypotension, two further readings are taken in the standing position, immediately, and after 3 min [23]. Once eligibility is confirmed, the participant then completes the trial questionnaires including the Illness Perception Questionnaire (symptom list) [24], Multimorbidity Treatment Burden Questionnaire [25], Katz Activities of Daily Living (ADL) - Life Ability Questionnaire [17], and Beliefs about Medicines Questionnaire (BMQ) General [15] and the EQ-5D-5L [16] which will give an interpretation of quality of life. Also included is an adapted variant of the Client Service Receipt Inventory [26] to measure health economic burden, the Free-Cog [27] to assess cognition, and the Attitudes Towards Deprescribing Questionnaire [28] to determine patient perception of medication reduction. Once these questionnaires have been completed to the best of their ability, they are then randomised into the trial by the person performing the baseline procedures. Stratified randomisation is used to individually allocate participants (1:1) to one of the two trial groups using a fully validated web-based randomisation system (Sortition) with stratification factors age (i.e. 75–79 and ≥ 80 years) and region of England. Randomly permuted block sizes is used within strata.

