### Follow-up

All participants (regardless of randomised group) are asked to return to their GP practice approximately 4 weeks following the baseline visit to have their blood pressure checked, and to report any adverse events that may have occurred. To ensure the safety of participants, blood pressure readings are taken in person. For those in the intervention arm whose blood pressure remains well controlled up to a target blood pressure of < 150 mmHg (or < 140 mmHg for those 75–79), the person performing the visit refers to the medication reduction plan and deprescribes a further antihypertensive if indicated. If another medication is deprescribed, participants are asked to attend a further safety visit 4 weeks later. This is repeated until there are no further antihypertensives to deprescribe, or until the GP/prescriber or participant feel it is inappropriate to deprescribe further. If participants’ blood pressure has risen above target at the safety visit, site staff are advised to invite them for another visit 1 week later to recheck their blood pressure. If the readings are still above threshold, further monitoring or re-prescribing of withdrawn medication is at the clinician’s discretion.

All follow-up after the safety visits are conducted remotely. Patient-reported outcomes are collected via questionnaires completed 1 year after participant’s baseline visit, which are either sent via email or post depending on individual participant preference. Clinical outcome data is extracted from electronic health records using three approaches. Firstly, primary care data is collected directly from participant’s records via a purpose-built database search run in each participating practice at the end of follow-up. Secondly, all participants are linked using unique trial identifiers, NHS number, and one other identifier (date of birth) to data held by NHS England. This includes Hospital Episode Statistics (the commissioning dataset that captures hospital activity such as diagnoses, procedures and therapies nationally) and Civil Registrations of Death, as provided by the Office of National Statistics. Thirdly, where possible and appropriate, primary care data is extracted remotely from the electronic health records of participants registered at primary care sites contributing to the Oxford Clinical Informatics Digital Hub (ORCHID).

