### Statistical methods for primary and secondary outcomes

The primary analysis will be according to randomised treatment assignment and will include all randomised participants for whom data are available, as defined by protocol eligibility criteria. Deprescribing antihypertensive medication will be deemed non-inferior to usual care in terms of death or emergency hospital admission if the lower limit of a 95% confidence interval for the absolute risk difference between usual care and medication reduction groups is above − 5%, i.e. if the percentage of emergency hospitalisations/deaths in the deprescribing group is less than 5 percentage units higher than in the usual care group. This primary outcome will be analysed using a generalised linear mixed effects model. The response will be a binary indicator of whether the participant experienced death or emergency hospitalisation at 1 year. The model will include age and NHS England region as fixed effects and site as a random effect. Any covariates found to be predictive of missingness in the outcome, through fitting univariate logistic regression models, will be included in the model.

Generalised linear models adjusting for age as a fixed effect and site as a random effect will be used for secondary outcomes e.g. differences in the proportions of patients with serious falls, serious hypotension, syncope, fracture, hospitalisation/death, any non-serious adverse event, ADWE, all-cause death, major cardiovascular events, stroke, MI and perceived side effects to antihypertensive at 12 months, differences in mean change in treatment burden score, number of prescribed medications, number of prescribed antihypertensives, blood pressure, quality of life at 12 months.

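### The symptom outcome is tied to the Beliefs about Medicines Questionnaire, while the only instrument labelled a symptom list is attached to no outcome

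*Protocol article*

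**What the plan says.** In the Protocol article, Trial outcomes, one secondary outcome is the between-group difference in the percentage of participants with "symptoms such as dizziness, fatigue and ankle swelling, using the Beliefs about Medicines Questionnaire (BMQ) General". The sentence names the instrument and gives it reference 15.

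Baseline assessments describes the "trial questionnaires including the Illness Perception Questionnaire (symptom list"), with reference 24. Later in the same list comes "and Beliefs about Medicines Questionnaire (BMQ) General [15] and the EQ-5D-5L [16"]. The two are therefore separate questionnaires with separate references, both completed before randomisation.

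Follow-up says only that "Patient-reported outcomes are collected via questionnaires completed 1 year after" the baseline visit, without listing the instruments. Statistical methods for primary and secondary outcomes includes "perceived side effects to antihypertensive at 12 months" among the proportions to be compared and names no instrument for it.

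**The concern.** An outcome definition should name a source that can supply the outcome. Here the outcome is the presence of physical symptoms, and the named source is, by its title, a questionnaire about beliefs. The same battery holds an instrument labelled as a symptom list, which the outcomes section never mentions.

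Two things are at stake. Anyone who follows the outcome definition literally would look for dizziness, fatigue and ankle swelling in a questionnaire that does not appear to record them. In addition, the trial is open-label and the outcome is self-reported, so its source should be fixed in public before results are known. If the published protocol names one instrument and the report uses another, the change may look as if it was made after the fact, even when it only corrects a slip.

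**Working it through.** No arithmetic applies, because the point depends on no event rate, margin, power or sample size. The check is to set the statements side by side.

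| Section of the article | Symptom outcome | BMQ General | Illness Perception Questionnaire |
|---|---|---|---|
| Trial outcomes | Defined as a percentage with symptoms | Named as its source (ref. 15) | Not mentioned |
| Baseline assessments | Not mentioned | Listed as a questionnaire (ref. 15) | Listed, marked as a symptom list (ref. 24) |
| Follow-up | Not mentioned | Not mentioned | Not mentioned |
| Statistical methods | Perceived side effects at 12 months, as a proportion | Not mentioned | Not mentioned |

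1. **Is it a citation slip?** No. Reference 15 accompanies the BMQ General in both places, and the Illness Perception Questionnaire has its own reference, 24. The outcomes section really does name the BMQ General.

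2. **Could the two names mean one instrument?** No. Baseline assessments lists them separately, with other questionnaires between them.

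3. **Are the neighbouring assignments sound?** Yes. In the same part of Trial outcomes, the EQ-5D-5L is paired with health-related quality of life and the Katz questionnaire with physical disability. Each pairing fits the instrument's title. The symptom pairing is the one that does not.

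4. **Does another section repair it?** No. The statistical section names no instrument. Its perceived side effects item is probably the same outcome, but the article does not say so.

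5. **Is the symptom list documented at 1 year?** Not in this article. The health economic section places the EQ-5D-5L at baseline and 12 months and the Client Service Receipt Inventory at follow-up. The Illness Perception Questionnaire appears only among the baseline procedures.

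6. **What is left over?** The symptom list is collected with no outcome attached to it, and the BMQ General has no stated use other than as the source of symptoms.

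7. **What else could change?** The primary outcome comes from linked hospital and death records and practice-reported events, and the sample size rests on that outcome. Neither uses any questionnaire.

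**The case against.** The strongest reply is that this is a condensed article. Protocol version 3.0 is not shown and may well assign symptoms to the symptom list and beliefs to the BMQ General. The sentence in Trial outcomes runs blood pressure, symptoms and the BMQ together, which fits a lost phrase. This stands as the likely cause, and it means that trial conduct may be unaffected. It does not remove the point: the article is not silent on the instrument but names one that does not match its own description elsewhere.

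A second reply is that the article leaves other instruments unmapped. The Free-Cog and the Attitudes Towards Deprescribing Questionnaire are not named in Trial outcomes, and treatment burden is an outcome with no instrument beside it. That also stands. The absence of the Illness Perception Questionnaire from the outcomes section would be no finding by itself. The point rests on the positive assignment to the BMQ General.

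A third reply is that the article does not describe the BMQ General's items and nowhere says that the Illness Perception Questionnaire supplies the symptom outcome. This is correct. Both steps are inferences, from a title and from a label.

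A reader might go further and infer that a belief score will be analysed as symptom prevalence while the symptom data go unused. The documents do not support this. The endpoint is worded as a percentage with symptoms, the statistical section treats perceived side effects as a proportion, and no section plans to analyse a belief score in their place.

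**Conclusion.** The inconsistency is real and should be corrected. One pre-specified secondary outcome is assigned to an instrument that does not appear to measure it, and the only instrument labelled as a symptom list has no outcome.

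The conclusion assumes that the BMQ General's title describes its content, and that the symptom-list label identifies the intended source. Both are reasonable, but the article confirms neither.

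The size should not be overstated. A reader might infer that symptom data are lost for all 3,014 planned participants, but nothing shows any loss of data. Nor does the article present symptom relief as a main expected benefit: its research questions concern admissions and death, then costs and quality of life, and symptoms are one item in a long secondary list. It is better read as a probable drafting slip in an outcome definition than as a deliberate choice of instrument.

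**What to change.** - In Trial outcomes, name the Illness Perception Questionnaire symptom list as the source of the 12-month symptom percentages. If another instrument was intended, name that one instead.
- Confirm that the symptom list is part of the 1-year questionnaire.
- State separately what the BMQ General is used for.
- In the analysis of each symptom, adjust for the same symptom at baseline. The stated models for secondary outcomes adjust for age and site only, and the baseline symptom list is already collected. This improves the analysis and is separable from the correction itself.
- Say whether perceived side effects in the statistical section is the same outcome, and use one name for it throughout.

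The cost is a few words in the outcomes section and one covariate per symptom model. No new baseline data are needed. If the symptom list turns out not to be in the 1-year questionnaire, it would have to be added for participants who have not yet reached that point, and the outcome would be limited for those who have.

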### Recruitment

The population of interest is adults aged ≥ 75 years with controlled systolic blood pressure (< 140 mmHg if aged 75–79 years or < 150 mmHg if aged ≥ 80 years), receiving two or more antihypertensive medications and at higher risk of serious adverse events. Potentially eligible participants are identified through a specially designed search tool incorporating the trial inclusion and exclusion criteria, run through general practice electronic health records.

#### Inclusion criteria

Willing and able to give informed consent for participation in the trial (or with personal legal representative consent)Willing and able to report any safety concerns or with a suitable carer able to report these if unableRegistered at either a practice using electronic health record systems (e.g. EMIS or SystmOne) or contributing to or willing to contribute to The Oxford Clinical Informatics Digital Hub ORCHID [18].Aged 75 years or above at recruitment.Controlled systolic blood pressure, defined (in accordance with NICE 2019 guidelines) [9] as less than 140 mmHg (if aged 75–79 years) or less than 150 mmHg (if aged 80 years or above). Systolic blood pressure level will be based on screening measurements taken at baseline (mean of the 2nd and 3rd readings taken in a standardised manner) [19] or from patient records if a face-to-face baseline visit is not possible.Prescribed two or more antihypertensive medications for at least 12 months prior to trial entry. Antihypertensive medications defined as any ACE inhibitor, angiotensin II receptor blocker, calcium channel blocker, thiazide and thiazide-like diuretic (including loop diuretics), potassium-sparing diuretic, alpha-blocker, beta-blocker, vasodilator antihypertensives, centrally acting antihypertensives, direct renin inhibitors, adrenergic neurone blocking drugs.Stable dose of antihypertensive medications for at least 4 weeks prior to trial entry.Moderate or severe frailty (defined by an eFI score ≥ 0.20) [20] and/or high risk (> 5%) of hypotension, syncope or falls in the next 5 years, based on STRATIFY risk prediction algorithms [21, 22] applied to an individual’s electronic health record.

